### 3.4. Study Tools

Signs of viability of embedded fleas will be determined using a handheld digital video-microscope with a 3 mega-pixel optical resolution. In addition, clinical photographs should be taken before and after treatment. If a child has another skin disease with tungiasis, we shall keep a record of it, since we will observe a combination of the skin diseases.

The following forms will be printed and used in the field to collect data:− Questionnaire for study participants: a structured questionnaire;− Case observation/record form;− Adverse event/effect record form.

To investigate seasonality associated with the research environment, we will also use a thermometer and hygrometer for assessment.

### 3.5. Data Collection and Storage

Data will not be collected on the names and affiliations of the participants. If they wish to discontinue the interview, observation, and treatment, their decision will be respected without any objections. Participation of school children in this study is totally voluntary. Since this is a school-based study, consent will first be obtained from each school. Informed consent will then be obtained from each participant, in accordance with the Ottawa Statement, an international guideline for cluster-randomised trials. For lesions not studied, dimeticone will be applied later, if desired. The area to be observed will be marked with an oil-based pen and photographed with a smartphone. Video recordings with a smartphone will be made only at the time of intervention, to confirm the intervention method. During the treatment, skin symptoms will be monitored until the final decision on the 7th day, using a checklist. Lesions will be examined and staged according to the Fortaleza classification [2], and counted (live/dead). The cure rate will be calculated at each stage, and significant differences at each stage will be tested. Participants will be observed and queried about adverse effects, and the severity score will be used to assess symptoms of acute tungiasis, including pain and itching. Feeling and ease of each treatment will be assessed using a questionnaire. Trained nurses will monitor the participants, and interviews will be conducted under the guidance of a medical doctor at treatment initiation and during the final decision. 

### 3.6. Pre-Study

A cohort study will be conducted as a pre-study to confirm the efficacy rates. The method is the same as in this non-inferiority trial, and 124 (62 in each cohort) lesions will be enrolled in the study.

## 4. Expected Results

Based on the results of previous studies, the treatment of tungiasis is not sustainable for rural communities. In this study, the primary endpoint will be the cure rate on day 7, following treatment with either 5% sodium carbonate solution or dimeticone, while the secondary endpoints will be differences in adverse effects and acute-pathology scores on day 7, as well as differences in feeling and ease on day 7. Therefore, this study can contribute toward designing a locally sustainable management-cycle that will improve the cure rate, reduce the scores of adverse effects and acute pathology, and sustain the acceptable local treatment for children in Kenya. We hope to help adopt new treatments into the national guidelines of Kenya. The treatment will be cheaply available locally and accessible to poor families suffering from tungiasis in this study area.

### 4.1. Statistical Analysis

For the primary outcome, logistic regression analysis (stepwise regression) will be performed, because it is binary. Since all secondary outcomes are score data, they are continuous measures; thus, analysis of covariance will be performed using two variables (sex (male or female) and footwear use (shoes or sandals)) as covariants. This is because previous studies have shown that the male sex is a risk factor for tungiasis, and that the thickness of the skin of the foot may change depending on whether sandals are used, which may affect the penetration of the treatment [32]. We will use generalized estimating equations for side effects such as pain and itching, to consider relative risks. The per-protocol set, which analyses only subjects who adhere to treatment, is more likely to show superiority or a significant increase in risk, while the intention-to-treat analysis is more likely to show non-inferiority with or without significant differences. Therefore, a per-protocol approach will be adopted for this non-inferiority study. All data will be analysed using EZR version 1.60 (Jichi Medical University Saitama Medical Center, Saitama, Japan). Missing values will be imputed using the multiple-imputation method. For the main analysis, we will use one-sided *p*-values at an *α* = 0.025 level of significance; for others, we will use two-sided *p*-values at an *α* = 0.05 level of significance.

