**Hypothesis:** 
*In this study, we hypothesise that the topical risk-difference of 5% sodium carbonate is no more than 10% non-inferior to dimeticone (NYDA^®^) when used in the treatment of tungiasis.*

Figure 1 shows the non-inferiority margin and the relationship with 95% confidence interval (95% CI) of the difference between experimental and control groups. If the risk difference of cure rate (95%CI) is greater than −10%, it can be shown than 5% sodium carbonate is not inferior to NYDA^®^.

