### 2.3. Study Design

The study will utilise a randomised design, compared to standard treatment intervention. Figure 3 shows the flowchart of this study. It will have two arms: treatment of embedded sand-flea infestations with 5% sodium carbonate, versus dimeticone. Randomisation will be performed according to treatment. A non-inferiority design is chosen, since it would be unethical to withhold an existing treatment that has demonstrated efficacy. This study will not measure any environmental intervention; therefore, we can measure only efficacy, not effectiveness. All participants will receive both treatments, one on each foot. Therefore, it is not possible to blind participants and interveners to treatment-group assignments. The study will be conducted during the dry season, when the prevalence of tungiasis is known to be at its peak, and at a time not impacted by holidays.

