### 2.7. Non-Inferiority Margin Settings

Initially, we would apply the fixed-margin method recommended by the Food and Drug Administration; however, there is insufficient data to estimate the risk ratio of standard intervention [26]. The European Medicines Agency [27] has indicated that “In such situations, it will be difficult to specify delta using the considerations outlined above; however, the best efforts should still be made to produce an indirect confidence interval for the new product against placebo using whatever data exist for the reference.” From this regulator’s view, it is best to consider delta somehow by using indirect data when studying treatments with no evidence of comparison to a placebo. Therefore, we decided to apply a method of determining margins based on scientific theory.

The risk ratio is superior to the risk difference in terms of robustness to differences in rates of outcome between previous studies and non-inferiority studies [28]. In addition, the risk difference is considered an index when analysing binary categorical data. Since the risk ratio is commonly used when performing a time-to-event analysis, the non-inferiority margin was set, based on the risk ratio.Estimating the risk ratio of standard intervention:

Since there is no placebo comparison of either 5% sodium carbonate or dimeticone, we will estimate whether the treatment group shows the same results as those reported by [29].2.Setting the risk difference of standard intervention using the lower limit of the effect estimate:

95%CI: −0.563 to −0.299.3.Setting the retention rate and calculating the non-inferiority margin (Wangge et al. [30]):

1 − ε = 0.67

Δ = (1 − 0.67) × −0.299 = −0.09867.

4.Range of interpretation: ±10%.

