### 2.8. Sample-Size Calculation

Based on the hypothesis, there is a difference between treatment with 5% sodium carbonate, with a 70% cure rate [14], and dimeticone, with a 78% cure rate [15]. Although it depends on the result of the pilot study, we would like to calculate the sample size assuming that both cure rates are 80%. The sample size was calculated using the method proposed by Schoenfeld [31], assuming a non-inferiority margin of 10% (δ = 0.1) and that the true mean cure-rates of the treatment agent (sodium carbonate) and the active control (NYDA^®^) are 80% (pT = 0.80) and 80% (pC = 0.80), respectively. We calculate the optimum sample needed to achieve 90% power (1 − β = 0.9) at the 5% level of significance (α = 0.05) with equal allocation (*k* = 1) for demonstrating non-inferiority for the clinical-cure assessment of efficacy. Since one to five lesions per foot will be studied per participant, the intra-class correlation coefficient (ICC) (1, *k*) with *k* = 2–5, would be used to evaluate the intra-rater reliability of the values, yielding an estimated ICC = 0.5. As the cluster size is two, the design effect is calculated as 1 + (2 − 1) × 0.5 = 1.5. A total of 920 (460 per arm) lesions will be recruited, considering a 10% rate of loss to follow-up. 

Before conducting this non-inferiority trial, a cohort study will be conducted as a pre-study. The sample size is estimated to have an 80% efficacy rate, absolute precision is 10%, and therefore 62 lesions are enrolled in each concurrent, parallel-treatment cohort.

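### The primary analysis, a stepwise logistic regression, neither estimates the risk difference that the verdict depends on nor accounts for paired feet and clustered lesions

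*Protocol article*

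**What the plan says.** The decision rule is in the Hypothesis section: "If the risk difference of cure rate (95%CI) is greater than −10%, it can be shown than 5% sodium carbonate is not inferior" to NYDA. Section 2.8 sizes the trial on the same scale, with δ = 0.1 and cure rates of 80% in both arms, and applies a design effect of 1.5 (ICC 0.5, cluster size two).

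Section 2.7 says that "the non-inferiority margin was set, based on the risk ratio", but its arithmetic starts from an interval labelled as a risk difference and ends at "Δ = (1 − 0.67) × −0.299 = −0.09867".

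On structure, Section 2.3 states: "All participants will receive both treatments, one on each foot". Section 3.1 (Stage 4) selects one to five lesions per foot.

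On analysis, Section 4.1 states: "For the primary outcome, logistic regression analysis (stepwise regression) will be performed, because it is binary". The same section sets a one-sided 0.025 level for the main analysis and names a correlated-data method only for other outcomes: "We will use generalized estimating equations for side effects such as pain and itching, to consider relative risks". It does not list the candidate covariates for the primary model and does not say that treatment stays in it.

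**The concern.** Three faults sit in one sentence of Section 4.1.

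- **Scale.** The verdict needs a risk difference, Section 2.7 speaks of a risk ratio, and the named model yields an odds ratio. Nothing links them. The usual p-value from a logistic model tests an odds ratio of 1, not a shifted null at the margin, so the one-sided 0.025 test has no stated non-inferiority hypothesis to act on.
- **Correlation.** Lesions lie within feet, and feet are paired within children. The sample size recognises correlation and the side-effect analysis uses GEE, but the primary model has no GEE, random effect, conditional form or robust variance.
- **Selection.** Stepwise selection chooses terms from the data. The nominal confidence interval then no longer has its stated coverage, and nothing prevents the treatment term from being dropped.

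The trial is meant to inform national guidelines (Section 4). Its main conclusion would rest on the wrong quantity and the wrong standard error.

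**Working it through.** **1. Scale behind the sample size.** Inputs from Section 2.8: cure 0.80 in both arms, margin 0.10, power 90%, α = 0.05 (read as one-sided), design effect 1.5, loss 10%.

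- Variance term: 0.8 × 0.2 + 0.8 × 0.2 = 0.32.
- n = 0.32 × (1.645 + 1.282)² / 0.10² = 274.04, so 275 per arm.
- 275 × 1.5 = 412.5, so 413; 413 / 0.9 = 458.9, so 459 per arm.

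This reproduces the stated 460. The trial is therefore sized for a risk-difference comparison that allows for clustering. (One-sided 0.025, the level in Section 4.1, would give 563 per arm; that is a separate matter.)

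**2. Odds ratio against −10 points.** At 80% control cure, −10 points means 70% v 80%:

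OR = (0.70/0.30) / (0.80/0.20) = 0.583.

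Holding that odds ratio at other control rates:

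| Control cure | Treated odds | Treated cure | Risk difference |
|---|---|---|---|
| 70% | 0.583 × 0.70/0.30 = 1.361 | 57.6% | −12.4 points |
| 78% | 0.583 × 0.78/0.22 = 2.068 | 67.4% | −10.6 points |
| 80% | 0.583 × 0.80/0.20 = 2.333 | 70.0% | −10.0 points |
| 90% | 0.583 × 0.90/0.10 = 5.250 | 84.0% | −6.0 points |

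Conversely, −10 points corresponds to an odds ratio of 0.667 at 60% control cure, 0.599 at 78%, 0.444 at 90% and 0.298 at 95%. No single odds ratio stands in for the margin.

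**3. Ignoring pairing and clustering.** With m lesions per foot, correlation ρw between lesions on the same foot and ρb between lesions on a child's two feet (equal variances in the arms), the true variance of the treatment difference divided by the variance under independence is

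V = 1 + (m − 1)ρw − mρb.

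A nominal one-sided 0.025 test then has a true level of 1 − Φ(1.96/√V). Here ρw = 0.5 is the ICC in Section 2.8; ρb is not given, so it is varied from 0 to 0.5.

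| m | ρb | V | True one-sided level |
|---|---|---|---|
| 2 | 0 | 1.5 | 0.055 |
| 2 | 0.25 | 1.0 | 0.025 |
| 2 | 0.5 | 0.5 | 0.003 |
| 5 | 0 | 3.0 | 0.129 |
| 5 | 0.25 | 1.75 | 0.069 |
| 5 | 0.5 | 0.5 | 0.003 |

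**4. Simulation at the margin.** True cure was 70% v 80%, with 460 lesions per arm and 4,000 trials per case. A latent-normal model had total child-plus-foot correlation 0.7, which is about 0.47 on the binary scale. The table shows how often non-inferiority was falsely declared at nominal 2.5%. The naive test is a risk-difference test that treats lesions as independent; the alternative is a paired analysis of child-level differences.

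| Lesions per foot | Correlation | Naive | Paired by child |
|---|---|---|---|
| 2 | foot only | 5.4% | 2.5% |
| 2 | split | 3.1% | 2.7% |
| 2 | child only | 0.4% | 2.5% |
| 5 | foot only | 13.2% | 2.7% |
| 5 | split | 7.1% | 2.7% |
| 5 | child only | 0.6% | 3.7% |

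Two further simulations with slightly different settings put the five-lesion, foot-only case at 11.9% and 14.1%. None of them includes stepwise selection, so its effect is not quantified here.

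**The case against.** The best defence is that the estimand is clear elsewhere. The Abstract says proportions of dead fleas will be compared, the Hypothesis section gives the risk-difference rule, and a logistic model can yield a risk difference by standardisation. A condensed article may leave that step, and the variance method, to the analysis plan. This is right to the extent that logistic regression is not in itself incompatible with the rule. But Section 4.1 does not leave the method open. It names one, with stepwise selection, and followed as written that method gives no risk difference.

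It is also fair that the protocol never calls lesions independent; that is inferred. The inference is strong, because the same section names GEE for side effects and nothing comparable for the primary outcome.

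The sizes can be challenged too. The protocol proposes no odds-ratio margin, and at its own expected control rates of 78% to 80% the drift is at most 0.6 points. The highest error rates need five lesions on every foot and no correlation between feet. At two per foot, with correlation split between child and foot, the naive test is close to nominal, and with child-level correlation it is conservative. All of this stands. It limits how bad the error is likely to be but does not show which case applies, because the protocol does not say how its ICC divides between foot and child.

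That stepwise selection might remove the treatment term is a possibility left open by the text, not something it states.

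**Conclusion.** The concern holds. As written, the primary analysis does not deliver the quantity compared with −10 points, does not handle pairing or clustering, and uses data-driven selection in a confirmatory test.

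The scale fault is small near 80% control cure and material away from it: 2.4 points too lenient at 70% and 4 points too strict at 90%, if the odds ratio matching the margin at 80% were used. The standard-error fault can go either way. False non-inferiority runs from about 0.3% to about 13% against a nominal 2.5%, assuming a within-foot ICC of 0.5, two to five lesions per foot and a between-feet correlation of 0 to 0.5. The upper end means wrongly accepting sodium carbonate; the lower end means an over-wide interval and lost power. This must be corrected before analysis.

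**What to change.** In Section 4.1, replace the primary-outcome sentence with a pre-specified analysis:

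- **Estimate:** the marginal risk difference in day-7 cure, sodium carbonate minus dimeticone.
- **Model:** GEE with identity link, or logistic GEE followed by standardisation, clustered on the child with robust standard errors. Clustering on the child covers both the pairing of feet and the lesions within each foot.
- **Terms:** treatment always in the model, and any covariates fixed in advance. The baseline Fortaleza stage of the lesion is a natural candidate, since Section 3.1 already records it. Delete the stepwise procedure.
- **Rule:** claim non-inferiority if the lower limit of the two-sided 95% interval exceeds −10 points, which matches the one-sided 0.025 level already stated.

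In Section 2.7, correct the text to say that the margin is a risk difference, as its own arithmetic and Section 2.8 imply.

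The cost is a change of wording. No new data or visits are needed; the robust variance may call for a package beyond the software's standard menus.

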We will sample participants with a smaller number of lesions sides, and select one to five embedded sand-fleas per foot. Because it is difficult to distinguish the characteristics of individual lesions [15], we will limit the number of lesions studied. The growth level of the target lesions should be stage II or III, according to the Fortaleza classification [2]. Only lesions that can be clearly distinguished from one another with viable embedded sand-fleas will be included in the study. Lesions will be chosen such that their location will make it possible to use a handheld digital microscope. Each lesion will be photographed and circled with a marker, and its location and stage noted in the patient’s record.

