### 3.2. Randomisation, Allocation, and Blinding

All study participants will receive 5% sodium carbonate and dimeticone, with one treatment per foot. Randomisation will be carried out at the treatment level and not the individual level. Trained nurses will perform the intervention. It is not possible to blind the intervener administering the treatment because 5% sodium carbonate will require soaking the foot, whereas NYDA^®^ will be applied directly to each lesion. As the two treatments will not change the skin colour of the feet, the principal investigator will be a blinded observer.

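### The primary model leaves covariates to stepwise selection, so baseline Fortaleza stage, which can differ between a child's two feet, may or may not be adjusted for; fixing it in advance would give a small gain in precision

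*Protocol article*

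**What the plan says.** Section 4.1 sets the primary analysis: "For the primary outcome, logistic regression analysis (stepwise regression) will be performed, because it is binary". It gives no candidate list and names no term to be kept regardless of selection. The only covariates it names, "two variables (sex (male or female) and footwear use (shoes or sandals)) as covariants", belong to the analysis of covariance for the secondary scores.

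The design is within child. Section 3.2 states: "All study participants will receive 5% sodium carbonate and dimeticone, with one treatment per foot".

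On stage, section 3.1 (Stage 4) limits entry: "The growth level of the target lesions should be stage II or III, according to the Fortaleza classification". It has each lesion "circled with a marker, and its location and stage noted". Section 3.5, straight after its sentence on Fortaleza staging, adds: "The cure rate will be calculated at each stage, and significant differences at each stage will be tested". Section 3.1 (Stage 3) places lesion sampling before randomisation. No section matches or balances stage between the feet.

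**The concern.** Treating one foot each way balances whatever the two feet share: sex, footwear, age, school. It does not balance the stage mix of the one to five lesions studied on each foot. Of the covariates discussed here, the one that pairing leaves unbalanced is therefore the one whose use depends on a selection step.

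Two things follow. First, if stage predicts day-7 viability, leaving it out gives up precision that could be had from data already collected. Second, the form of the primary model is decided by the trial's own results. An odds ratio from a logistic model also changes with the covariates retained, whereas the Hypothesis judges non-inferiority on a risk difference against −10%.

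**Working it through.** **1. The plan's own sample size.** Inputs from section 2.8: cure 80% in both arms, margin 10 points, power 90%, 5% significance, design effect 1.5, 10% loss.

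- n = (1.645 + 1.282)² × 2 × 0.80 × 0.20 / 0.10² = 275 per arm after rounding up.
- 275 × 1.5 = 412.5, and 412.5 / 0.9 gives 459, against 460 stated. The figure reproduces if the 5% is one-sided.
- At the one-sided 0.025 of section 4.1, 337 × 1.5 / 0.9 gives 562. That mismatch is a separate matter.

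**2. Precision without stage.** Evaluable lesions per arm: 460 × 0.9 = 414. Effective number: 414 / 1.5 = 276.

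- SE = √(2 × 0.16 / 276) = 0.03405.
- Power at one-sided 0.025 = Φ(0.10 / 0.03405 − 1.96) = 83.6%. At one-sided 0.05 it is 90.2%.

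**3. Chance imbalance in stage.** Assume a stage III share q = 0.5 and apply the same design effect to stage; the documents give neither.

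- SD of the between-arm difference in stage share = √(2 × 0.25 / 276) = 0.0426.
- 1.96 × 0.0426 = 0.083, or 8.3 points, reached or exceeded in about 1 trial in 20, both directions together.
- Shift in the crude difference = 0.083 × stage gap in cure.

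**4. Gain from fixed adjustment, compared with no adjustment.** Variance removed R² = q(1 − q) × gap² / 0.16. Adjusted SE = 0.03405 × √(1 − R²). The gap is assumed.

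| Assumed stage gap | Shift at 1.96 SD | Variance removed | Power unadjusted | Power adjusted |
|---|---|---|---|---|
| 5 points | 0.4 points | 0.4% | 83.6% | 83.7% |
| 10 points | 0.8 points | 1.6% | 83.6% | 84.1% |
| 20 points | 1.7 points | 6.3% | 83.6% | 85.8% |

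**5. Sensitivity.**

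- With q = 0.3, the variance removed is 0.3%, 1.3% and 5.3%, and adjusted power is 83.7%, 84.0% and 85.5%.
- With stage independent across all lesions, the SD is √(0.5 / 414) = 3.5 points, and the shifts are about 0.3, 0.7 and 1.4 points.
- A simulation of 207 children with two lesions per foot gave a mean error of about 0 with and without adjustment. For gaps of 10 and 20 points the variance removed was 1% and 6% with stage independent between lesions, and 2% and 13% if both lesions on a foot share a stage.

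**6. What stepwise selection would do.** Suppose stage is a candidate and is kept at p < 0.05; the protocol states neither. The stage contrast has 2 × 414 / 1.5 = 552 effective lesions, 276 per stage, so its SE is again about 0.03405. For gaps of 5, 10 and 20 points the expected z is 1.5, 2.9 and 5.9, and Φ(z − 1.96) gives retention of about 31%, 84% and nearly 100%. Stage would mostly be dropped only where dropping it costs about 0.4% of the variance.

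**The case against.** The strongest reply is that this is one reviewer's preferred covariate, and that a covariate list is commonly left to the analysis plan. The absence of a list would indeed be no finding. But section 4.1 does more than stay silent: it chooses stepwise selection for the primary non-inferiority model, and that choice can be judged as it stands.

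A second reply is that stepwise selection would pick up stage whenever it matters. This largely stands if stage is a candidate, as step 6 shows. The protocol does not say that it is, and even then the model remains data-dependent.

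A reader might also infer that stage imbalance biases the comparison, especially as lesions are chosen so that the microscope can be used on them. The documents do not support this. Lesions are sampled before the sealed envelope decides which foot gets which treatment, so the imbalance is chance. The shifts in step 4 are part of ordinary sampling error, which a valid interval already covers; they are not an addition to it.

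A reader might likewise infer a large loss of power. At an assumed gap of 30 points the formula gives 83.6% against 88.6%. But no such gap is documented, and there a stage candidate would almost always be retained.

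Finally, section 3.5 plans cure rates and tests by stage, so stage-specific results would be visible. That is fair, but separate tests within stages are not a stage-adjusted primary estimate.

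**Conclusion.** The point holds as a low-cost improvement, not as a fault that invalidates the comparison. Baseline stage is recorded for every studied lesion, is not balanced by the within-child design, and may or may not enter the primary model.

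The size is small: about 0.4% to 6% of the variance and about 0.1 to 2 points of power at one-sided 0.025, for fixed adjustment compared with none. The variance gain could reach about 13% at a 20-point gap if lesions on one foot share a stage. Compared with stepwise selection it is smaller if stage is a candidate. The mismatch in alpha between sections 2.8 and 4.1 costs more, 90.2% against 83.6%.

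The figures rest on assumed stage gaps of 5 to 20 points, an even split between stages, and a design effect taken from the outcome. If stage does not predict day-7 viability, there is no precision to gain, and only the data-dependence of the model remains.

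**What to change.** In section 4.1, replace stepwise selection for the primary outcome with a prespecified model containing treatment and the baseline stage of each lesion (II or III) as fixed terms. Take stage from the pre-treatment record described in section 3.1, not from a reading during follow-up: section 3.5 describes staging together with the live/dead count, and a stage read after treatment could itself be affected by treatment. From that model report the stage-standardised risk difference with a 95% CI that accounts for clustering by child, and compare its lower limit with −10%. Showing the stage mix per arm beside it would let readers see any imbalance.

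The cost is a line or two of analysis wording. No new data are needed.
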